### 3.8. Procedures

#### 3.8.1. Study Schedule

|                                                                                                                                                                                                                                                                                                                              | First Study Visit
(Screening and
Baseline Visit) | Baseline Period
(approx. 3 weeks)* | Intervention (Length
depends on treatment) |
|------------------------------------------------------------------------------------------------------------------------------------------------------------------------------------------------------------------------------------------------------------------------------------------------------------------------------|--------------------------------------------------------|---------------------------------------|-----------------------------------------------|
| Frequency of
each Measure                                                                                                                                                                                                                                                                                                 |                                                        | Daily                                 | Treatment Session                             |
| Oura Ring (~60
rings available)                                                                                                                                                                                                                                                                                           | ✓                                                      | ✓                                     | ✓                                             |
| Intake Form                                                                                                                                                                                                                                                                                                                  | ✓                                                      |                                       |                                               |
| REDCap Data Collection                                                                                                                                                                                                                                                                                                |                                                        |                                       |                                               |
| GAD-7                                                                                                                                                                                                                                                                                                                        | ✓                                                      |                                       | ✓                                             |
| PHQ-9                                                                                                                                                                                                                                                                                                                        | ✓                                                      |                                       | (✓)                                           |
| MADRS                                                                                                                                                                                                                                                                                                                        | ✓                                                      |                                       | (✓)                                           |
| 
GAD-7 – Generalized Anxiety Disorder – 7-item Scale
 
PHQ-9 – Patient Health Questionnaire – 9-item Scale
 
MADRS - Montgomery-Asberg Depression Rating Scale
 
✓ - Assessment or data collection relevant to all treatment arms.
 
(✓) - Assessment included in some treatment arms but not all.
 |                                                        |                                       |                                               |

**Note:** As per IPP clinic protocol, patients undergoing rTMS will have their GAD-7 and PHQ-9 self-report responses entered after each treatment session, whereas patients undergoing IVK or ECT treatment will not complete the PHQ-9 (i.e., only the GAD-7 will be entered on REDCap) and will instead complete the MADRS with a member of the clinical team at each treatment session.

### ***3.8.2. Recruitment***

Patients who have been referred to the IPP to receive rTMS, IVK or ECT treatment will be recruited to participate in this study. An individual from the program's clinical team will inform newly referred patient-participants that either one or two digital platforms – the REDCap platform and (if eligible and available) the Oura Ring wearable device – are available to facilitate the collection of data. The collection of active data will allow researchers to evaluate longitudinal changes in self-report cognitive-behavioural symptoms; passive data will allow participants to monitor their own data in real-time which can have a positive impact on their health since it can promote healthy behaviours. If patients are interested in participating, the clinical team will direct potential participants to a member of the research team, who will provide more information about the study and obtain informed consent (see Appendix E).

### ***3.8.3 Informed Consent***

Potential patient participants who are interested in the study will be emailed an informed consent form (ICF) and contacted by a member of the research team to discuss study details and answer any questions the participant may have. The ICF will clearly state to interested patients that their data will be de-identified for the wearable device (Oura Ring) and that the study team is not able to discuss any mental health concerns with them. Participants will have the opportunity to discuss any questions about the study with the Study Coordinator. They will also have the option to speak with the Principal Investigator, whose contact information will be provided in the ICF. Once the patients have carefully read through the ICF, they will then be asked to confirm their interest and return a digitally signed copy to the research team. A member of the research team will then verify and confirm each patient's enrollment and eligibility.

### ***3.8.4 Screening and Baseline Visit (30 - 60 Minutes)***

Upon receiving digital consent, the first visit (which will constitute a Screening and Baseline Visit) will be scheduled by the clinical team. Participants will sign a hard-copy of the ICF in-person, complete baseline measures of general anxiety (Generalized Anxiety Disorder Scale, GAD-7) and depression (Patient Health Questionnaire, PHQ-9; or Montgomery-Åsberg Depression Rating Scale, MADRS), and their Oura account will be set-up(if applicable). For participants receiving an Oura Ring, the Screening and Baseline Visit will take place in-person (at the Interventional Psychiatry Program at St. Michael's Hospital) at least three weeks before the start of their clinical treatment so they can receive a properly-fitting device and complete a baseline recording period to establish a reliable baseline for passive data collection and Oura's app features. More specifically, a member of the study team will determine the participant's ring size (using an Oura sizing kit); provide the appropriate device; assist participants in downloading, setting up, and using the Oura app on their smartphone using their assigned de-identified credentials (de-identified email address and password); and answer any questions the participant might have. In contrast, this visit will occur on the first treatment day for participants who are not receiving the Oura Ring (i.e., REDCap only), as part of clinical care.

### ***3.8.5 Intervention***

#### ***3.8.5.1 Standard of Care***

Participants will receive the standard treatment protocol for one of the clinical treatments offered at the IPP for TRD (rTMS, IVK, and ECT). During clinical visits, participants will complete self-report questionnaires (GAD-7, PHQ-9), and may complete a clinician-administered assessment of depression (MADRS), as part of clinical care; assessment administration and frequency in the IPP is dependent on the treatment arm. The clinical team will enter participants' responses to these measures into REDCap after each treatment session. The Columbia-Suicide Severity Rating Scale (C-SSRS) may also be collected by the clinical team to continuously assess for suicidality while participants are in treatment; however, the C-SSRS will not be used as an outcome measure for this study.

### 3.8.5.2. Digital Intervention Data Collection

#### 3.8.5.2.1. Active Data – Self-Report Questionnaires via REDCap

For active data collection, a member of the clinical team will enter patient-participants' self-report questionnaire and (if applicable) clinical assessment responses directly into the REDCap platform at the end of each study visit and treatment session (Appendix A). Active data will be used in combination with passive data – activity, sleep, and physiological data – for correlation and prediction of the clinical landmarks of response, remission, and depressive relapse.

As per IPP clinic process, participants will complete the following assessments on each treatment session day (approximately 10 - 30 minutes):

1. Anxiety: Generalized Anxiety Disorder - 7-item scale (GAD-7)
2. Depression: Patient Health Questionnaire- 9-item scale (PHQ-9) or Montgomery-Asberg Depression Rating Scale (MADRS)

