The last treatment arm in the IPP comprises ECT, which is reserved for patients who fail to respond to rTMS and IVK. ECT is a safe and effective treatment for several mental health conditions, including depression, bipolar disorder, and schizophrenia, which have not improved from other treatments. Also, it may be considered the most effective treatment modality in psychiatry and with robust anti-suicidal effects. ECT involves administering a brief, controlled electrical current between two electrodes applied on the surface of the scalp or temple. The current stimulates a specific part of the brain and causes a small, controlled seizure which lasts between 15 and 90 seconds, and the whole procedure is performed under general anesthesia.

In this study, we will be assessing the uptake and feasibility of using a web-based platform (Research Electronic Data Capture – REDCap) and a wearable device (Oura Ring) to collect data from adults receiving treatment for TRD, using the following metrics: number of recruitments, recruitment rates, dropout rates and reasons for dropping out, and data completion rates. In addition, by collecting dynamic digital (active and passive) data, we will be able to analyze this data with respect to treatment response, remission, and relapse rates for each treatment arm. Treatment response is defined as a 50% or greater decrease in clinical symptoms (as captured by clinical assessments or self-report scales: MADRS, GAD-7, and PHQ-9); remission is defined as clinical assessment scores below the clinical threshold (e.g., MADRS  $\leq 10$ ); and relapse is characterized by the recurrence of symptoms after a patient has achieved remission (e.g., MADRS  $\geq 20$  after initial remission).

There are concerns that the use of digital platforms may affect the therapeutic relationship, yet there is a paucity of studies exploring this impact. A prior study focused on the effects of Information & Communication Technologies (ICT) in two culturally distinct countries, and the authors reported that the increased deployment of ICT facilitated patient empowerment.

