## **2.2. Objectives**

This project aims to determine the feasibility of utilizing digital platforms to collect active and passive data related to mental health symptoms among adult outpatients with TRD receiving clinical treatment at the IPP and evaluate the association between the digital data collected with the treatment outcomes of relapse, remission and response. The proposed digital platforms include (1) a wearable device (Oura Ring) to capture passive data on activity, sleep and physiological parameters, and (2) a web-based clinical data management platform (REDCap) to capture responses to validated clinical scales (PHQ-9 and GAD-7) and clinical assessments (MADRS, intake form, demographics) conducted as part of patient care.

The REDCap platform will be available to all participants enrolled in this study; this platform will enable the clinical team to record participants' self-reported symptoms in an electronic platform outside the medical electronic health records system for use in research. Oura Ring use

will be optional and will depend on: 1) device availability, 2) participant's interest, and 3) participant's ownership of a smartphone compatible with the Oura App (to sync and visualize data). We anticipate that approximately 60 Oura Rings will be available for participants to use. Participants will be able to visualize their passively captured data (e.g., activity, sleep parameters, heart rate, respiratory rate, body temperature) on the Oura App in near real-time. These data streams have the power to enable a fine-grained understanding of a patient's experience through means of continuous data collection, visualization, and self-monitoring.

This study has the following aims:

- **Primary Aim:** To examine the feasibility of a digital suite (REDCap clinical scales and a wearable device; Oura Ring) to collect active and passive data, respectively, among adults receiving clinical treatment at the IPP for TRD.
- **Secondary aims:**
  - To evaluate the association of active data (from REDCap) and passive data (from the Oura Ring) over the duration of clinical treatment with the outcomes of treatment response (reduction of  $\geq 50\%$ ), remission (score  $\leq$  clinical threshold), and relapse (score  $\geq$  clinical threshold after initial remission).
  - To create personalized digital phenotype profiles (pDPPs) based on wearable and web-based data.

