### **3. METHODS**

#### **3.1. Study Design**

This observational study with retrospective data analysis will assess the feasibility of multimodal digital platforms to collect active (self-report) and passive (wearable biometrics) data and enable self-monitoring of adult patients receiving clinical treatment for TRD. Specifically, we will assess the feasibility of using a web-based electronic data capture platform (REDCap) and a wearable device (Oura Ring) to collect active and passive data, respectively, in tandem with neuropsychiatric treatment for TRD in the IPP. The overall duration of this study is three years. However, each participant will only be enrolled in this study for the duration of their clinical treatment in the IPP. All participants will begin participation during the first study visit (known as the Screening and Baseline Visit), which will take place upon scheduling of the first treatment session. For participants receiving the Oura Ring, the Screening and Baseline Visit will occur in-person (so they can obtain an Oura Ring) and will take place approximately three weeks before the first treatment session, to establish baseline parameters measured by the Oura Ring. For participants not receiving the Oura Ring, their clinical treatment can begin after the

Screening and Baseline Visit (usually ~0-3 weeks after), therefore, some participants may complete these measures at their first treatment session .

Following REB approval, 200 patients aged 18 years or older will be recruited over 33 months and will have their self-report assessments (GAD-7 and, if applicable, PHQ-9) entered on the REDCap platform for use in research (see Appendix A). Depending on the availability of Oura Ring devices, a subset of participants will also be offered the opportunity to use an Oura Ring, which is a wearable device that will collect data on sleep, activity, and physiological data in near real-time during their participation in this study. We estimate that approximately 60 Oura Ring devices will be available for participants to use. Potential participants will be adults with TRD enrolled for clinical treatment at the IPP at St. Michael’s Hospital, Unity Health Toronto (SMH-UHT). Participants will receive one of the clinical treatments at the IPP according to clinical protocols and standard of care (Figure 1). The details of the study design are summarized in Figure 2.

[figure not shown]

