| Secondary Outcome | 
Clinical outcomes will be measured by:
 
 
a) Quantifying changes in active (self-report) and passive (physiological) data over time
 
b) Predicting treatment response , remission, and relapse based on active (self-report) and passive (physiological) data .
 
                                                                                                                                                                                                                                                                |

|  |                                                                                                       |
|--|-------------------------------------------------------------------------------------------------------|
|  | c) Constructing personalized digital phenotype profiles (pDPPs) based on wearable and web-based data. |
|--|-------------------------------------------------------------------------------------------------------|

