## **5.4. Sample Size Considerations**

This project aims to collect pilot data on the feasibility of the REDCap platform and the Oura Ring wearable device to collect data of adult outpatients receiving clinical treatment for TRD; therefore, a sample size of 200 participants should provide enough power for pilot quantitative analysis across treatment arms. We have followed the sample size calculator for digital phenotyping studies developed by Barnett et al.

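### The first secondary aim names only yes/no outcomes for the ring association, although depression is scored at every session; with about 60 wearers this could cost about 15 to 25 points of power

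*Protocol*

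**What the plan says.** Section 2.2 sets the first secondary aim as the association of active and passive data "with the outcomes of treatment response (reduction of" at least 50%), remission (at or below a threshold) and relapse (at or above a threshold after remission). The trial summary repeats this. Section 2.1 gives the definitions: "Treatment response is defined as a 50% or greater decrease in clinical symptoms", with a MADRS of 10 or less as the example of remission and 20 or more after remission as the example of relapse.

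Secondary outcome b in section 3.7 reads "Predicting treatment response , remission, and relapse based on active (self-report) and passive (physiological) data". Section 3.8.5.2.1 states the use of the combined data in the same terms: "for correlation and prediction of the clinical landmarks of response, remission, and depressive relapse". The same section says "participants will complete the following assessments on each treatment session day", listing GAD-7 together with PHQ-9 or MADRS. The note to the schedule in 3.8.1 assigns PHQ-9 to rTMS and MADRS to IVK and ECT.

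Uncut data are used elsewhere. Secondary outcome a is "Quantifying changes in active (self-report) and passive (physiological) data over time", and section 5.1 lists correlation, regression and multilevel modelling for it.

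On numbers, section 3.1 says "We estimate that approximately 60 Oura Ring devices will be available for participants to use", and section 3.8.5.2.2 has returned rings cleaned and passed to further participants. Section 5.4 says "a sample size of 200 participants should provide enough power for pilot quantitative analysis across treatment arms" and gives no correlation, event rate, significance level or power.

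**The concern.** Response and remission are cuts of a multi-point score. A patient whose score falls by 49% counts the same as one who does not change, and one whose score falls by 51% counts the same as one who recovers fully. Most of the gradation in improvement is therefore lost before it is related to sleep, heart rate or activity. Ring use is optional and limited by device supply, so this association is likely to rest on well under the full 200 participants and has little precision to give away. Section 7 intends the outcome-prediction results as pilot data for more definitive studies. A real but moderate ring signal could be missed at that stage although the finer score is already in REDCap.

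**Working it through.** The protocol states no power figure for this aim, so there is none to reproduce. The check compares the power of one ring feature against a continuous depression score with its power after that score is cut into yes/no.

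**Inputs from the protocol**
- About 60 devices (2.2, 3.1, 3.6.2), reissued after return (3.8.5.2.2).
- Target of 200 participants (3.1, 5.4).
- Maximum dropout 30% (3.7).

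**Assumptions not in the protocol**
- Two-sided 5%, one feature, one score per person, bivariate normal.
- True correlation r of 0.25 to 0.45.
- Share p of responders or remitters of 30 to 50%.

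**Formulas**
- Power = Φ(√(n−3)·atanh(r) − 1.96) + Φ(−√(n−3)·atanh(r) − 1.96).
- Cutting at share p multiplies r by φ(z_p)/√(p(1−p)): 0.798 at 50%, 0.759 at 30%.

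**Worked case: n = 60, r = 0.35**
- Uncut: √57 × atanh(0.35) = 7.550 × 0.3654 = 2.759; Φ(2.759 − 1.96) = 78.8%.
- Cut at 50%: r becomes 0.35 × 0.798 = 0.279; power 58.2%.
- Cut at 30%: r becomes 0.35 × 0.759 = 0.266; power 53.8%.
- A bivariate-normal simulation (20,000 runs) gave 79.2%, 59.4% and 54.8%.

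**Grid at n = 60**

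| r | Uncut | Cut, 50% events | Cut, 30% events |
|---|---|---|---|
| 0.25 | 48.7% | 33.3% | 30.5% |
| 0.30 | 64.7% | 45.3% | 41.7% |
| 0.35 | 78.8% | 58.2% | 53.8% |
| 0.40 | 89.2% | 70.4% | 65.8% |
| 0.45 | 95.5% | 81.0% | 76.6% |

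Before rounding, the loss runs from 14.6 points (r = 0.45, 50% events) to 25.0 points (r = 0.35, 30% events). Outside this grid, at n = 60 and 30 to 50% events, it is 10 to 12 points at r = 0.20, 9 to 13 at r = 0.50 and 2 to 4 at r = 0.60. In information terms a 50% cut keeps 0.798² ≈ 0.64, so 60 people count as about 38.

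**Other numbers of wearers (r 0.25 to 0.45, 30 to 50% events)**

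| Wearers analysed | Loss in points |
|---|---|
| 42 (60 × 0.70, after maximum dropout) | 11 to 26 |
| 120 (rings reissued) | 2 to 24 |
| 200 (everyone) | 0 to 18 |

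Weaker signals still lose at the largest size: with n = 200 and r = 0.20, 81% falls to 62% (50% events) or 57% (30% events).

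**What the check leaves out.** Relapse is conditional on an earlier remission and is not a simple cut of a change score, so these figures do not apply to it. The multi-feature models and the repeated-session model were not given a power figure.

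**The case against.** A reader might infer that the protocol throws the uncut scores away. It does not. Section 2.1 speaks of exploring the association between active and passive data as something separate from predicting clinical outcomes. Section 5.1 treats the active data as the reference standard for the passive data and plans models for distress and depression. Sections 2.2.1 and 5.2 build individual models joining physiology to questionnaire responses. None of these carries a cut. This stands, and it confines the point to the wording of one aim. It does not remove the point, because none of these places names the continuous depression score as the outcome to which ring data are related under that aim.

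Ranking secondary analyses can be left to an analysis plan that is not shown here. That is fair for model detail. The form of the outcome, however, is set in the protocol's own aim and outcome sections.

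A reader might also take 60 as the size of the ring group. It is a count of devices that are reissued during 33 months of recruitment, so there may be more wearers and a smaller loss.

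Percentage response gives one definition across PHQ-9 and MADRS, and this is a real advantage. Analysing each scale separately would give it up and could do worse than the cut: with 30 wearers per scale and r = 0.35, √27 × 0.3654 = 1.899 and power is about 48% per scale, against 58.2% for the pooled 50% cut. A remedy must therefore pool the arms.

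Finally, a reader might infer that a missed association would fail the study. The stated thresholds concern recruitment, dropout, data completion, loss to follow-up and compliance; none depends on a ring association.

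**Conclusion.** The point holds for the first secondary aim, secondary outcome b and section 3.8.5.2.1: each names only binary landmarks although a depression score exists at every session. The cost is about 15 to 25 points of power for a single feature if about 60 people wear a ring, the test is two-sided 5%, the correlation is 0.25 to 0.45 and 30 to 50% respond or remit. None of those conditions comes from the protocol except the device count, and the loss shrinks with more wearers or a stronger signal. The figures cover response and remission, not relapse, and do not measure the gain from a repeated-session model. This is an exploratory secondary aim in a feasibility pilot, so the change is a worthwhile and cheap improvement, not a flaw in the primary objective.

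**What to change.** In 2.2, 3.7 b and 3.8.5.2.1, add the continuous depression score as the main outcome for the ring association. Standardise it within scale (PHQ-9 for rTMS, MADRS for IVK and ECT) so that all arms enter one model. Adjust for the baseline score on the same scale and for treatment arm, using the regression or multilevel model that 5.1 already lists. Keep response, remission and relapse as reported supportive outcomes.

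The cost is a wording change and one more model on data already collected, with no new visits or participants. The downside is small: the main result is in standardised units, less direct than a clinical landmark, and it assumes that the two scales are comparable once standardised. Reporting the landmarks beside it keeps the clinical reading.
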